### Data collection and management

2.11

Data collection will be conducted by assessors at each clinical site who are independent of both intervention delivery and statistical analysis. All scale-based assessments will be performed in separate rooms to ensure privacy and reduce bias. Assessors, who are blinded to the participants’ group allocation, will undergo standardised training and will provide only necessary clarifications on assessment tools, without influencing participant responses. At each assessment time point, both assessors and participants will be limited to the specific scale being administered. Participants will complete their sleep diaries and promptly submit them to the assessors. Actigraphy data will be downloaded and analysed by trained assessors using ActiLife software.

Recognising the challenges of ensuring accurate and complete self-recording of sleep diaries and actigraphy data, a comprehensive compliance strategy will be implemented. This includes in-person training at baseline on the use of sleep diaries and actigraphy devices, with reinforcement sessions at weeks 4 and 8. A robust monitoring protocol will also be in place, whereby assessors will routinely verify data completeness and accuracy, providing immediate feedback and reminders to participants as needed.

All study data will be initially documented in standardised, paper-based Case Report Forms (CRFs) and subsequently entered into a web-based Electronic Data Capture (EDC) system. Double data entry will be employed to minimise errors. Data entry personnel at each site will remain uninvolved in other trial procedures and will have access only to data from their respective centres. An independent Data and Safety Monitoring Board (DSMB) will oversee data integrity and safety. If discrepancies arise, a data supervisor will issue a query form to the responsible researcher for clarification. If required, the statistician may also initiate a query. All responses will be recorded on the query form, which will then be returned to the statistician by the trial inspector.

### Statistical analysis

2.12

Statistical analyses will be conducted using SAS version 9.4 (SAS Institute, Cary, NC). Descriptive statistics will be reported as mean ± standard deviation (Mean ± SD) for normally distributed continuous variables with homogeneous variance, and as median with interquartile range [Median (P25, P75)] for non-normally distributed or heteroscedastic data. Categorical variables will be presented as frequencies and percentages. All analyses will follow the intention-to-treat (ITT) principle. Missing data due to participant dropout will be handled using the last observation carried forward (LOCF) method.

Baseline characteristics, including demographic variables and hypnotic medication use before and after the intervention, will be analysed as follows: Continuous data with normal distribution and homogeneity of variance will be assessed using the independent two-sample t-test; otherwise, the Mann–Whitney U test will be applied. Categorical variables will be analysed using the chi-squared test. For the primary and secondary outcome measures, repeated measures will be analysed using a linear mixed-effects model. Fixed effects will include intervention group, time, and their interaction (intervention × time), while a random intercept for each participant will be included as a random effect. Results will be reported as point estimates with 95% confidence intervals. All statistical tests will be two-sided, with a *p*-value < 0.05 considered statistically significant.

To assess potential heterogeneity in treatment effects and enhance the generalisability of the findings, exploratory subgroup analyses will be conducted based on key baseline characteristics. In particular, we will examine whether the primary and selected secondary outcomes differ among participants with common age-related comorbidities such as hypertension and diabetes. These analyses will be exploratory in nature and are intended to inform hypothesis generation for future studies.

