### Sample size calculation

2.6

The sample size was determined based on the primary outcome: change in PSQI score from baseline to Week 8. A superiority trial design employing a two-sample mean comparison was used to assess whether EA demonstrates clinically meaningful superiority over SEA. Based on prior reports of the minimal clinically important difference (MCID) for PSQI in traditional Chinese medicine trials (1.69–1.80) (43, 44), the superiority margin(*δ*) was set at 1.8. The sample size per group (n) was calculated using the formula (45):

$$n=[{\left(z_{1-\alpha }+z_{1-\beta }\right)}^{2}\sigma^{2}(1+1/K)]/{\left(\in -\delta \right)}^{2}.$$

where: n is the sample size of per group, σ is the estimated standard deviation, ϵ is the difference between treatment and control group, δ is the superiority margin.

Based on a prior single-centre RCT, PSQI scores decreased by 5.67 in the EA group and 1.83 in the SEA group, yielding ϵ = 3.8 (33). Therefore, we set ϵ = 3.8, assumed a standard deviation σ = 4, a one-sided significance level α = 0.025 (z_1 − α_ = 1.960), a type II error *β* = 0.1 (z_1 − β_ = 1.282), and an allocation ratio K = 1 (1:1 allocation between the experimental and control groups).

The calculated sample size per group is n = 85. Accounting for a 20% attrition rate, the final sample size is adjusted to 107 participants per group, resulting in a total enrolment target of 214 older adults with insomnia disorder.

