## Discussion

3

Age-related alterations in sleep–wake cycles and circadian rest-activity rhythms often present as fragmented nocturnal sleep and excessive daytime sleepiness in older individuals (65). While multiple clinical guidelines recommend non-pharmacological therapies—particularly CBT-I—as the first-line treatment (16, 17), accessibility to CBT-I remains limited in regions such as China (66), and its efficacy in elderly populations requires further substantiation. Consequently, hypnotic medications remain the primary treatment for insomnia disorder in older adults. However, diminishing therapeutic effects and concerns over adverse outcomes associated with long-term use warrant alternative therapeutic strategies. Acupuncture, a widely utilised non-pharmacological intervention, lists insomnia among its principal indications and is a promising avenue of research (67, 68). Nevertheless, definitive evidence on its efficacy and safety in older adults is lacking, necessitating rigorously designed, adequately powered multicentre randomised controlled trials—such as the present study. Insomnia disorder is now widely recognised as a distinct clinical entity that warrants independent diagnosis and treatment, irrespective of comorbid conditions (42). An expanding body of empirical evidence supports the effectiveness of insomnia-specific interventions even in the presence of comorbidities (69). Given the complex health profiles of older adults, many of whom present with chronic illnesses, we have implemented exclusion criteria to eliminate confounding conditions such as other sleep disorders, neuropsychiatric illnesses, cancer, or other life-threatening diseases. However, we have not excluded individuals with stable chronic diseases. This decision is based on two considerations: the high prevalence of chronic conditions in this population, which should be balanced across groups through randomisation; and the need to ensure ecological validity by maintaining a sample representative of the broader population of older adults with insomnia. As this is not a pharmacological trial, participants may either be using hypnotic medications regularly or not at all, provided their insomnia symptoms are chronic and stable, and they agree not to increase their medication use after enrolment. To ensure baseline equivalence, pre-enrolment hypnotic use will serve as a stratification factor. This inclusion criterion is consistent with acupuncture research conventions (30, 70, 71) and permits a meaningful evaluation of acupuncture’s therapeutic effect. Based on expert clinical consensus and our prior research, we have selected the acupoints and EA parameters for this trial. Fixed acupoints, derived from traditional Chinese medicine theory and clinical practice, include GV20, GV24^+^, EX-HN22, HT7, PC6, CV12, CV4, ST36, and SP6. In addition, following standard clinical acupuncture practice (72), acupuncturists will select adjunctive acupoints tailored to individual symptoms commonly observed in older adults with insomnia, potentially enhancing treatment efficacy. Given the typically prolonged duration and increased severity of insomnia in older adults, the intervention phase will last 8 weeks, with sessions conducted thrice weekly. A 12-week post-intervention follow-up will assess sustained effects. Assessments will occur at baseline, weeks 4 and 8 of intervention, and weeks 4 and 12 post-intervention (i.e., study weeks 12 and 20), allowing for the evaluation of both short-term and long-term outcomes. This follow-up structure aligns with previous randomised controlled trials investigating acupuncture for other forms of insomnia (30, 32, 70).

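### LOCF for dropout is imposed before a mixed model that needs no imputation under missing at random; it can bias the PSQI difference in either direction, by an amount that depends on who leaves and when

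*Protocol article*

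**What the plan says.** All of this is in the protocol article; the statistical analysis plan is not shown.

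- Section 2.12 (Statistical analysis) sets the analysis principle, "All analyses will follow the intention-to-treat (ITT) principle", and one rule for dropout: "Missing data due to participant dropout will be handled using the last observation carried forward (LOCF) method".
- The same section names the model: "For the primary and secondary outcome measures, repeated measures will be analysed using a linear mixed-effects model". Its fixed effects are group, time and their interaction, and "a random intercept for each participant will be included as a random effect".
- On testing it says: "All statistical tests will be two-sided, with a *p*-value < 0.05 considered statistically significant". It names no margin.
- Section 2.6 (Sample size calculation) sizes the trial on "change in PSQI score from baseline to Week 8", with a superiority margin of 1.8 PSQI points. It then allows for loss: "Accounting for a 20% attrition rate, the final sample size is adjusted to 107 participants per group". It does not say when in the 20 weeks that loss occurs.
- PSQI is assessed at weeks 0, 4, 8, 12 and 20 (Table 1). The Discussion gives the purpose of the later visits: "A 12-week post-intervention follow-up will assess sustained effects".

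**The concern.** The two instructions in section 2.12 work against each other. A linear mixed model fitted by likelihood uses whatever visits each participant has, and is valid under missing at random without filling anything in. LOCF first replaces each missing visit with a copy of the last score and hands it to the model as if it had been measured. That swaps the missing-at-random assumption for the assumption that a dropout's score stays where it was.

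That assumption fits this trial poorly. The design expects scores to move during the 8-week course, and the follow-up exists to learn whether benefit lasts once treatment stops. LOCF answers that second question by assumption for everyone lost after week 8.

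Three things are at stake: the size of the primary week-8 difference, the honesty of its standard error, and the durability result at weeks 12 and 20. There is also a mismatch with section 2.6. Inflating for attrition treats dropouts as contributing nothing, whereas LOCF lets all 107 per arm enter as if complete.

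**Working it through.** **Inputs from section 2.6.** Expected difference 3.8 (prior changes 5.67 EA and 1.83 SEA), SD 4, margin 1.8, one-sided alpha 0.025, power 90%, 1:1 allocation, 20% attrition.

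**Assumed, because the document does not give them.** When dropouts leave, the fraction *f* of the full effect already present in the carried value, dropout by arm, and (in simulation) within-person correlation 0.5, a linear gain to week 8 and dropout unrelated to outcome.

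**1. The plan's own figure.** n = (1.960 + 1.282)² × 4² × 2 / (3.8 − 1.8)² = 84.08, rounded up to 85. Then 85 / 0.8 = 106.25, rounded up to 107. Both reproduce. Power is 0.903 with 85 per arm, and 0.905 with 107 × 0.8 = 85.6 completers.

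**2. When LOCF is unbiased for the difference.** Let *d* be the proportion lost in an arm and *m* the mean change its dropouts would still have shown between their last visit and the target visit. LOCF shifts that arm's mean change by −*d* × *m*. The difference is therefore unbiased only if *d* × *m* is equal in the two arms.

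**3. Week 8, equal dropout.** Expected difference = 3.8 × [1 − *d*(1 − *f*)]. SE = 4 × √(2/107) = 0.547. Power against the margin = Φ((difference − 1.8)/0.547 − 1.96).

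| Lost before week 8 | *f* | Difference | Power against 1.8 |
|---|---|---|---|
| 20% | 0 (baseline carried) | 3.04 | 0.62 |
| 20% | 0.25 | 3.23 | 0.74 |
| 20% | 0.5 | 3.42 | 0.84 |
| 20% | 0.75 | 3.61 | 0.91 |
| 20% | 1 | 3.80 | 0.955 |
| 10% | 0 | 3.42 | 0.84 |
| 10% | 0.5 | 3.61 | 0.91 |

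For 90% power the difference must be at least 1.8 + (1.960 + 1.282) × 0.547 = 3.57, a shrinkage of 6.0%. With *d* = 20% that requires *f* ≥ 1 − 0.060/0.20 = 0.70. Against zero, power is at least 0.9998 in every row.

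**4. Simulation of the random-intercept model** (3,000 runs per pattern, 20% dropout in each arm, week-8 result):

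| Dropout pattern | LOCF: mean, power against 1.8 | Observed data: mean, power against 1.8 |
|---|---|---|
| All before week 4 | 3.04, 0.67 | 3.81, 0.92 |
| Half before week 4, half in weeks 4-8 | 3.24, 0.78 | 3.80, 0.92 |
| All in weeks 4-8 | 3.41, 0.85 | 3.80, 0.93 |
| Even over 20 weeks | 3.52, 0.90 | 3.79, 0.94 |

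In the half-and-half pattern, the average model SE under LOCF is 0.516, while the estimates actually vary with SD 0.561. Part of the simulated LOCF power thus comes from an understated SE. For even dropout, the closed form gives a difference of 3.8 × (1 − 0.05 − 0.05 × 0.5) = 3.515 and power 0.88.

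**5. Week 8, unequal dropout, baseline carried.** With no true difference and both arms improving by *c*, the bias is *c* × (*d*SEA − *d*EA). For 10% EA and 30% SEA:

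- *c* = 1.83: 1.83 × 0.20 = 0.37; two-sided rejection 0.10
- *c* = 3.75, the midpoint: 0.75; rejection 0.28
- *c* = 5.67: 5.67 × 0.20 = 1.13; rejection 0.55

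The nominal rate is 0.05. Reversing the dropout rates reverses the sign. With the prior trial's changes, 30% EA and 10% SEA gives 5.67 × 0.7 − 1.83 × 0.9 = 2.32 and power 0.16 against the margin. The reverse gives 5.67 × 0.9 − 1.83 × 0.7 = 3.82 and 0.96.

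**6. Week 20, losses after week 8.** If a fraction *q* is lost right after week 8 and the true difference has fallen to *w*, LOCF shows (1 − *q*)*w* + 3.8*q*. With *q* = 20%: *w* = 0 shows 0.76, *w* = 1 shows 1.56, and *w* = 1.9 shows 2.28. In simulation with *w* = 0, two-sided rejection is about 0.31 if all 20% leave just after week 8, 0.19 if half leave after week 8 and half after week 12, and 0.12 if dropout is even over the 20 weeks. The observed-data model stays near 0.05.

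**The case against.** The strongest defence is that the harm is conditional, and this largely stands. A reader might infer that LOCF destroys the stated 90% power. The document does not support that: it gives no dropout timing, and power stays near 90% if losses are spread over 20 weeks or if carried values hold at least about 70% of the effect. The loss also concerns only the 1.8 margin. Section 2.12 describes an ordinary two-sided test without a margin, and against zero power is hardly touched. Whether the margin belongs in the analysis is a separate question.

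A reader might also infer that LOCF will manufacture a sustained benefit. That needs losses after week 8 and a true benefit that wanes. Those participants are not the ones who dilute week 8, so one 20% pool cannot produce both harms at full size.

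It is likewise too strong to say that LOCF is biased unless scores never change after dropout. Equal rate-weighted later change cancels in the difference. With equal dropout and a growing effect, the week-8 bias is towards less benefit. Nothing in the document predicts 10% versus 30% dropout: participants are blinded by a sham, and the retention measures apply to everyone.

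Two further points are fair. Missing at random is itself an assumption. And sensitivity analyses may sit in the unseen analysis plan, so their absence is not criticised here.

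What does not stand is a defence of LOCF as needed for intention-to-treat. With baseline kept among the repeated measures, the mixed model includes every randomised participant who has a baseline score. Nor does a tendency to be conservative rescue the rule, since the direction depends on dropout that nobody can know in advance.

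**Conclusion.** The point holds in conditional form. Section 2.12 positively prescribes LOCF as its dropout rule for a model that does not need it, so this is a poorly chosen stated rule and not omitted detail.

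- **Week 8, all 20% lost beforehand in both arms:** the expected effect is about 3.0-3.4 instead of 3.8, and power against the 1.8 margin about 62-85% instead of 90%, when carried values hold from none to half of the effect.
- **Week 8, unequal dropout:** bias in either direction. The spurious 0.37-1.13 points favouring EA assume 10% versus 30% loss, baseline carried and equal improvement of 1.83-5.67 in both arms. This harm affects the ordinary two-sided test and does not depend on the margin.
- **Weeks 12 and 20:** durability is overstated only if benefit truly wanes and participants are lost after week 8. The illustrative apparent effect at week 20 is 0.38-0.77 when the true effect is zero.

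Dropout timing, carried fraction, arm-specific dropout and within-person correlation are all assumptions. The sample size calculation is correct. Because the rule governs the primary estimate, it should be changed before unblinding.

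**What to change.** Remove LOCF from the primary analysis. Fit the mixed model already named, by REML, to all observed PSQI assessments with baseline among the repeated measures, and state that this assumes missing at random. Do the same for the other repeated outcomes.

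Suggested wording:

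> The linear mixed-effects model will be fitted by restricted maximum likelihood to all observed assessments without imputation, assuming data are missing at random. Sensitivity analyses will examine departures from this assumption.

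The analysis plan should hold a sensitivity analysis for data not missing at random, such as delta-adjusted or reference-based multiple imputation. If LOCF is kept at all, it should be a labelled sensitivity analysis beside that one. Dropout by arm and by visit should be reported, since these decide how far any missing-data method matters.

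The cost is a wording change and a little extra analysis in SAS, which the protocol already names. No new data are needed and 107 per group stands: the observed-data model gave about 0.92-0.94 power against the margin in the simulated patterns with 20% dropout.

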### Randomisation and blinding

2.7

Participant randomisation will be conducted via a centralised, web-based system. An independent statistician, uninvolved in trial execution, will generate the allocation sequence using SAS 9.4 software, employing stratified block randomisation with two stratification factors: study site and current use of hypnotic medication. Variable block sizes (2, 4, 6, or) will be used. Following confirmation of eligibility, designated randomization personnel at each study site will input the participant’s information into the central system to obtain a unique identification number and treatment allocation. Access to this system will be restricted to randomisation personnel and data monitors; all other study staff, including outcome assessors and statisticians, will remain blinded. Randomisation personnel will only be able to view participants and allocations within their respective centre.

This trial adopts a single-blind design, with participants blinded to group allocation. Due to the nature of EA, blinding of acupuncturists is not feasible. Participants will be informed during enrolment that they have an equal probability of being assigned to either intervention group. To ensure effective blinding, sham acupuncture needles with validated manufacturing standards and prior use in clinical trials will be used for the SEA group (35–37). Participants will undergo treatment in a supine position while wearing eye masks, and all interventions will be conducted in separate rooms to minimise cross-group contamination. Blinding integrity will be assessed at week 8, after the final treatment session, by asking participants to guess their group assignment. Apart from the acupuncturists administering the intervention, all other study personnel, including outcome assessors and statisticians, will remain blinded until the trial’s conclusion, at which point routine unblinding will be performed. All research staff will undergo comprehensive training prior to trial initiation and will strictly adhere to role separation protocols across departments.

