### Intervention

2.8

Both EA and SEA groups will receive standardised sleep hygiene education in accordance with the Chinese Guidelines for the Diagnosis and Treatment of Adult Insomnia (2017) (46), which includes the following recommendations: ① Avoid consumption of stimulants such as coffee, strong tea, or tobacco within 4–6 h before bedtime; ② Refrain from alcohol use before sleep, particularly as a sedative; ③ Engage in daily moderate physical activity, avoiding intense exercise within 3–4 h before bedtime; ④ Avoid overeating or consuming difficult-to-digest foods prior to bedtime; ⑤ Minimise exposure to stimulating activities, including watching television or reading emotionally arousing material, within 1 h before sleep; ⑥ Maintain a quiet, comfortable, and appropriately lit and temperature-controlled bedroom environment; ⑦ Establish and adhere to a consistent sleep–wake schedule.

Participants in both groups will receive 24 intervention sessions (30 min each), administered three times per week on alternate days over 8 weeks. During each session, participants will lie supine, with intervention areas exposed and eye masks worn to block visual stimuli. Licensed TCM practitioners with over three years of clinical experience, all of whom have completed standardised training specific to this trial, will administer either EA or SEA based on group assignment.

Participants already using hypnotic medications at baseline may continue their prescribed regimens but must record all medication usage. Dose escalation is prohibited unless approved by a psychiatrist. Participants not taking hypnotics at baseline will not be allowed to initiate or increase hypnotic use during the study. In the event of severe insomnia symptoms, such as persistent sleeplessness over multiple nights, participants may use emergency medication—zolpidem tartrate tablets (Stilnox, 5 mg; National Medicine Permit H20181237, Sanofi Winthrop Industrie)—and must document its use. Concurrent insomnia-related treatments, including dietary supplements, Chinese herbal medicines, and CBT-I, are not permitted during the trial.

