#### Hypnotic medication use

2.9.2.6

Participants will document their use of hypnotic medications in sleep diaries. Upon data collection, the proportion of participants using hypnotics in both groups before and after the intervention, as well as the proportion with increased or decreased dosages, will be calculated.

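### Post-intervention hypnotic use is compared by a chi-squared test that ignores baseline use, so this one measure of a secondary outcome is tested far below its nominal 5% level and loses power

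*Protocol article*

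**What the plan says.** The protocol article defines the outcome under Hypnotic medication use (2.9.2.6) as "the proportion of participants using hypnotics in both groups before and after the intervention, as well as the proportion with increased or decreased dosages". That gives two measures: use or non-use, and change of dose.

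Statistical analysis (2.12) handles the outcome together with the baseline table: "Baseline characteristics, including demographic variables and hypnotic medication use before and after the intervention, will be analysed as follows". For categorical data the method is "Categorical variables will be analysed using the chi-squared test". The same section adds "All analyses will follow the intention-to-treat (ITT) principle" and sets a two-sided 5% level. It mentions no stratification, adjustment or restriction to baseline users for this outcome.

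Two other sections bear on the choice. Randomisation and blinding (2.7) names "two stratification factors: study site and current use of hypnotic medication". Intervention (2.8) states: "Participants not taking hypnotics at baseline will not be allowed to initiate or increase hypnotic use during the study". The same section lets participants take emergency zolpidem for severe symptoms, and Table 1 lists that on its own row.

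**The concern.** Stratified randomisation makes the share of baseline users nearly equal in the two arms. A between-group test of the proportion before the intervention therefore tells the reader nothing.

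After the intervention, baseline non-users stay close to zero use by rule. Almost all random variation in the proportion using then comes from which baseline users stop. The plain chi-squared test takes its variance from the overall proportion as if baseline use varied freely between arms. That variance includes a between-stratum part that the design has removed, so the standard error is too large and the test too conservative. At stake is a null result on this measure that reflects the choice of test and not the data.

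**Working it through.** **The plan's own figure.** The article gives no size or power for hypnotic use. Its sample size for the primary outcome reproduces: (1.960 + 1.282)² × 4² × 2 / (3.8 − 1.8)² = 84.08, rounded up to 85 per arm; 85 / 0.80 = 106.25, rounded up to 107 per arm, 214 in total. The check below uses 107 per arm.

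**Denominator.** Among baseline users alone, the proportion using before the intervention would be 100%. The use measure therefore makes sense only over all participants, which also fits the intention-to-treat statement.

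**Assumed inputs.** Let q be the share of baseline users and s the share of users who stop. The article gives neither. Users are taken as balanced between arms, with no new users and no dropout.

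**Variance.** Per participant, and up to a common factor, the true variance of the arm difference in the proportion using is q·s·(1 − s). The plain test assumes p(1 − p) with p = q(1 − s). The ratio of true to assumed variance is

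q·s·(1 − s) / [q(1 − s)(1 − q(1 − s))] = s / (1 − q(1 − s)).

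The large-sample size of the test is 2·[1 − Φ(1.96 / √ratio)]. For q = 0.4 and s = 0.2, the ratio is 0.2 / (1 − 0.32) = 0.294, and 1.96 / √0.294 = 3.61, which gives a size of about 0.0003.

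**Size and power for the proportion using.** Size: 80% continue in both arms. Power: 50% (electroacupuncture) against 80% (sham) continue.

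| Baseline users | Power, planned test | Power, baseline users only | Power, dose decrease over all participants |
|---|---|---|---|
| 30% | 32% | 73% | 61% |
| 40% | 54% | 86% | 77% |
| 60% | 84% | 96% | 93% |

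Over these user shares the size of the planned test is about 0.03% to 0.15%, against about 5% among baseline users. The last column counts each participant who stops as a dose decrease. The size of that test is 3.2% to 4.2%.

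A smaller effect, 60% against 80% continuing, gives 16% against 54% (planned against users only) with 40% users, and 28% against 63% with 50% users.

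**One table as an example.** With 43 users per arm (40% of 107), suppose 22 and 34 continue:
- Over 107 per arm, the planned test gives p = 0.062.
- Over 43 users per arm, p = 0.007.
- Counted as decreases (43 − 22 = 21 against 43 − 34 = 9) over 107 per arm, p = 0.018.

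**Relaxing the assumptions.** All three cases stay at 50% users with 20% (sham) against 40% (electroacupuncture) stopping, except the last.
- With no new users and 214 participants, power is 28% for the planned test and 64% for a Cochran-Mantel-Haenszel test stratified by baseline use. With 170 completers it is 20% against 55%.
- If 5% to 10% of non-users count as users, for example through emergency zolpidem, the planned test has a size of 0.2% to 0.9% and power of 28% to 29%, against 46% to 57% for the stratified test. The gap narrows but remains.
- With 90% users of whom half stop, the variance ratio is 0.5 / (1 − 0.45) = 0.91, and the problem nearly disappears.

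**The case against.** The strongest reply is that the plan already holds a measure that would pick up a reduction. Section 2.9.2.6 also reports the proportion with a decreased dose. If those who stop count as decreases, a plain chi-squared test of that measure over all participants is only mildly conservative: 77% power against 86% with 40% users, and p = 0.018 in the example table. Partial reductions would count there as well. This stands. A reader might infer that the planned analysis misses real reductions in hypnotic use, or would probably report no difference when there is one. The documents do not support that for the outcome as a whole.

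The denominator for dose change is not stated, and baseline users would be a natural one. That also stands, so the criticism is confined to the use measure.

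Every magnitude rests on assumed user shares and stopping rates. This is true of the size of the loss but not of its direction, which follows from the stratification and the rule for non-users.

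A reader might also take reduced hypnotic use for a central aim of the trial. The stated objective is the efficacy and safety of electroacupuncture. The abstract does not list hypnotic use among the secondary outcomes, baseline users may keep their regimens, and the Discussion says this is not a drug trial.

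It could be said that such detail belongs in an analysis plan that is not shown. For this outcome, however, the article does name a test, and that test does not fit the design.

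**Conclusion.** The point holds for one measure of a secondary outcome: the proportion using hypnotics after the intervention. The planned test ignores a stratification factor that nearly determines that measure. With 107 per arm, 30% to 60% baseline users, no new users and no dropout, its size is about 0.03% to 0.15% instead of 5% when 80% continue in both arms. When 50% against 80% continue, its power is 32% to 84%, against 73% to 96% among baseline users. The loss is smaller if more participants are users, if more of them stop, or if emergency zolpidem counts as use.

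The error runs only against finding a difference. It creates no false positives and leaves the primary PSQI analysis and the sample size as they are. This is an improvement available at no cost, not a flaw that endangers the trial's main conclusion.

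**What to change.** In Statistical analysis (2.12), or in the analysis plan before unblinding:

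- Separate hypnotic use from the baseline table, and drop the between-group test of the proportion before the intervention. Describe it only.
- Compare post-intervention use by a Cochran-Mantel-Haenszel test or a logistic regression that includes baseline hypnotic use and site, or make the comparison among baseline users. Report a risk difference with a 95% confidence interval. If no baseline non-user is a user afterwards, the logistic model cannot estimate the baseline-use term, so the Cochran-Mantel-Haenszel test or the users-only comparison is the safer choice.
- State that the denominator for dose decrease is baseline users, and whether stopping counts as a decrease.
- Tabulate emergency zolpidem separately, by arm and baseline use, so that it does not enter the use measure unnoticed.

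The cost is wording only. Baseline use and site are recorded at randomisation, and no further data or participants are needed.
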